## Methods: Data collection, management and analysis

A separate data management plan will be created for the trial. The case report forms will be paper based. They will be collated and completed by the clinical trial co-ordinator and dedicated research nurse. A password protected database will be created on the ACCESS platform to allow speed of data entry.

The Chief Investigator will act as custodian for the trial data. The following guidelines will be strictly adhered to: Patient data will be anonymised*.*
All anonymised data will be stored on a password protected encrypted computer.All trial data will be stored in line with the Medicines for Human Use (Clinical Trials) Amended Regulations 2006 and the Data Protection Act and archived in line with the Medicines for Human Use (Clinical Trials) Amended Regulations 2006 as defined in the Kings Health Partners Clinical Trials Office Archiving SOP.

### Per protocol analysis

The primary endpoint of this study is pharmacodynamic and therefore time between study drug dose and prostatectomy is an important factor for evaluation of the primary endpoint. To minimize the effects of dose reductions and interruptions, the primary endpoint analysis will be based on a per protocol analysis. Evaluable patients are defined as:Received at least 21 days (3 weeks) of study drug between 1.5–2.0 g daily.Received study drug uninterrupted for the last 7 days prior to prostatectomy.

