To determine safety of metformin in this non-diabetic patient cohort.	Assessment of adverse events and laboratory evaluations.
To determine surgical toxicity.	Assessment of surgical-specific toxicities: time between biopsy and surgery, peri-operative bleeding, infection, rectal injury and length of hospital stay.
Exploratory Objectives and Endpoints	
To evaluate the effects of metformin on functional imaging of the prostate.	Difference in ^18^F Choline PET/MRI between baseline and post-treatment (prior to prostatectomy) in a separate non-randomised cohort of five patients with MRI positive disease receiving metformin.

Following informed consent (see Additional file 1: Appendix 1 for informed consent form) and screening, patients in the main study will be randomised and continue metformin or placebo for four weeks until the evening prior to radical prostatectomy. The five patients in the PET-MRI sub study will all receive metformin. In the event that surgery is scheduled for after this time point, patient will continue study drug for an additional one week. Prostate tissue (at baseline from biopsy and post treatment from prostatectomy) will be used for analysis of p-AMPK, p-ACC, FASN by immunohistochemistry and proliferation will be measured using ki67 and TUNEL in both groups.

Tissue metformin levels will also be assessed in baseline and post-treatment prostate tissue in the metformin-cohort. Each tissue specimen will be assessed by an experienced uro-pathologist to identify benign and malignant tissue. Patients will also be invited to consent for tissue storage in an HTA licensed Biobank. Additional translational studies may be undertaken based upon the results of the initial analysis as described in this protocol. Study drug safety will be assessed by recording adverse events.

The primary endpoint of this study is pharmacodynamic and therefore time between study drug dose and prostatectomy is an important factor. To minimise the effects of dose reductions and interruptions, the primary endpoint analysis will be based on a per protocol analysis. Evaluable patients are defined as:

-Received at least 21 days (3 weeks) of study drug between 1.5–2.0 g daily.

-Received study drug uninterrupted for the last 7 days prior to prostatectomy.

-A secondary analysis will include an intention-to-treat analysis.

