Radiological assessment: In a subgroup of 5 patients with MRI positive disease: ^18^ F Choline PET/MRI, which will be performed after 21+/− 2 days of metformin and prior to prostatectomy. A time point prior to 28 days is chosen to allow radiological assessment to be scheduled without interfering with surgery scheduling.
A pre-operative surgical visit should occur prior to surgery, as per standard of care and local policies.

Study week 4 (+/− 1 week) – prostatectomy:

Patients will undergo prostatectomy. This will occur at the end of week 4 (+/− 1 week). Study drug treatment will continue up until the evening before surgery until the patient is nil by mouth (as per local guidelines). In the events patients undergo surgery beyond 4 weeks from randomisation; study drug will be continued for an additional 1 week. Surgery should occur as per local policies.If clinically necessary, surgery can be brought forward or not performed (this should be discussed with the Chief Investigator). The case should be presented to a multidisciplinary team meeting before any other non-surgical treatment is given. These patients will not be included in the analysis as, in the absence of surgery, it will not be possible to assess for post-treatment tissue markers.
Tissue Collection: Formalin Fixed Paraffin Embedded tissue will be taken from the radical prostatectomy specimen

Follow up 8–10 weeks post operativelyClinical assessments:Symptoms directed physical examination, including ECOG performance status, weight, waist/hip ratio and vital signsMedications reviewAdverse events and complete Clavien Dindo assessment
Laboratory determinations: Blood tests taken within 2 days of post-operative visit for other purposes can be used as part of the post-operative visit: FBC, renal function, LFT, bone profile, PSA, testosterone.

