### Dosing regimen

In order to limit gastrointestinal side effects patients will be instructed to take study drug at doses increasing from:500 mg once a day (day 1–2)500 mg twice a day (day 3–4)1 g twice a day from day 5 onwards for 4 weeks until prostatectomy +/− one week

Study drug will be continued until the evening prior to surgery. Placebo will be dose escalated in the same way. Participants will be given these instructions verbally as well as written instructions at the start of their medication compliance diary.

Study drug doses should ideally be taken at the same time each day. Missed doses of the study drug may be taken later, provided that the time of dosing is at least 6 h before the next scheduled dose. If dosing is missed for one day for any reason, double-dosing should not occur the following day. Acute alcohol intoxication can increase the likelihood of the rare, but serious adverse event of lactic acidosis. Therefore, all participants will be advised to avoid alcohol for the duration of the trial. Patients participating in the non-randomised 18F PET/MRI cohort will receive metformin, which will be dose escalated as outlined above. All dose modifications and duration of treatment will be identical to the randomized cohort.

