**Fig. 1 Fig1:**
[figure not shown]
Trial Schema

**Table 5 Tab5:** Trial Flow Chart

Phase	Screening	Pre-surgery Treatment			Surgery	Post-surgery
Time point	≤14 days before baseline	Baseline Day 1 of treatment	Day 21 (+/- 2 days)	Day 28 (+/- 1 week) prior to surgery	Day 28 (+/- 1 week)	8-10^f^ weeks post-op
Informed consent	x					
Eligibility review	x	x				
Randomisation		x				
Medical History^a^	x					
Demographics	x					
Physical Exam	x	x	x	x		x
Vital signs^b^	x		x	x		x
ECOG PS	x	x	x	x		x
Height	x					
Weight	x			x		x
Waist/Hip ratio	x			x		x
Haematology	x		x	x		x
Biochemistry^c^	x		x	x		x
Fasting Glucose/Lipids	x			x		
PSA and Testosterone	x			x		x
HbA1c	x					
Whole blood and Serum save^d^	X			X		
Study Drug Administration		x	x	x		
Medication review	x	x	x	x		x
Compliance evaluation (diary and verbal)			x	x		
Adverse events (CTCAE v4)^e^		x	x	x		x
Paraffin embedded tissue sent to laboratory	x				x	
Prostatectomy					x	
MRI safety assessment^g^	x					
^18^F Choline PET/MRI^g^	x			X^e^		

^a^Full medical history, including history other disease, active or resolved, concomitant illnesses and cancer diagnosis

^b^Blood pressure, pulse rate and oxygen saturation, BM

^c^Renal profile, liver function tests, bone profile

^d^To be taken at selected sites only and according to the Trial specific SOP

^e^Clavien Dindo assessment to be completed at 8-10 weeks post operatively

^f^This review will coincide with routine post-operative review

^g^Only for the 5 subjects participating in the exploratory PET-MRI group

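### The 21-day dose rule that defines the primary per-protocol set does not fit the dosing and surgery schedule: adherent men operated on Days 21–25 cannot qualify, and the 50 per arm makes no allowance for it

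*Protocol article*

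**What the plan says.** The Per protocol analysis section states: "To minimize the effects of dose reductions and interruptions, the primary endpoint analysis will be based on a per protocol analysis". Trial design says the same. There are two conditions for evaluability: "Received at least 21 days (3 weeks) of study drug between 1.5–2.0 g daily" and "Received study drug uninterrupted for the last 7 days prior to prostatectomy". Trial design adds: "A secondary analysis will include an intention-to-treat analysis".

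Dosing regimen sets 0.5 g a day on Days 1–2 and 1 g a day on Days 3–4, then "1 g twice a day from day 5 onwards for 4 weeks until prostatectomy", plus or minus one week. Study drug stops the evening before surgery, and placebo is escalated in the same way.

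Table 5 counts from Day 1 of treatment, which is also the day of randomisation. It places the pre-operative visit at "Day 28 (+/- 1 week) prior to surgery" and gives the operation the same day and tolerance. Interventions says of surgery: "This will occur at the end of week 4", again with one week either way.

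Table 3 lists one reduced level, 500 mg twice daily. Withdrawal of patients admits men with long unsanctioned interruptions to the pharmacodynamic assessment after 21 days of treatment, with no dose floor. It also replaces men who withdraw before completing treatment until 90 per arm have completed. Sample size recruits 50 per arm.

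**The concern.** The rule that decides who enters the primary analysis was apparently written without counting the escalation days. On the flow-chart window, a man can take every dose, be operated on a permitted day and still not be per protocol. The dosing section implies a different window, and the withdrawal section uses a different 21-day rule. Two analysts could therefore build different primary sets from the same data.

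Two separate losses follow. Early surgery costs numbers. Dose reduction costs numbers too, and it is a post-randomisation event that the active drug may cause more often than placebo, so losses of this kind could unbalance the arms. Neither loss is allowed for in the sample size.

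**Working it through.** **Qualifying days.** Inputs: band reached on Day 5 and last dose on Day D − 1 (Dosing regimen); surgery on Days 21–35 (Table 5: 28 ± 7).

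Qualifying days = (D − 1) − 5 + 1 = D − 5.

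- D = 21, 22, 23, 24, 25 gives 16, 17, 18, 19, 20: not evaluable.
- D = 26 gives 21, the first day that qualifies.
- D = 28 gives 23; D = 35 gives 30.

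So 5 of the 15 permitted days fail with perfect adherence.

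**The other reading of Dosing regimen.** Four weeks counted from Day 5 covers Days 5–32, with surgery on Day 33. One week either way gives surgery on Days 26–40. The earliest case then has exactly 21 qualifying days and nobody adherent is excluded, but the window runs past the Day 35 limit in Table 5.

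**Dose reductions.** 500 mg twice daily is 1 g a day, below the 1.5 g floor. Days 5–25 make 21 days, so a reduced man qualifies only if the reduction starts on Day 26 or later (the dose tables describe no return to the higher level).

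**Holds.** Spare days = D − 5 − 21 = D − 26: 2 at Day 28 and 9 at Day 35. Holds of up to 7 days are permitted. A full 7-day hold after Day 4 needs D ≥ 33, with the last 7 days uninterrupted.

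**The plan's own sample size.** n per arm = 2σ²(z₀.₉₀ + z₀.₈₀)²/δ², two-sided alpha 0.20, with (1.2816 + 0.8416)² = 4.508.

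- Scenario 1: 2 × 35²/15² × 4.508 = 49.1, so 50.
- Scenario 2: 2 × 65²/30² × 4.508 = 42.3, so 43.
- Scenario 3: 2 × 25²/15² × 4.508 = 25.0 (just above 25), so 26.
- Scenario 4: 2 × 50²/25² × 4.508 = 36.1, so 37.

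All four match the alpha 0.20 column of Table 6. Scenario 1 sets the 50.

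**Power with fewer evaluable men.** Power ≈ Φ(δ/(σ√(2/n)) − 1.2816). For Scenario 1 at n = 50: 15/(35 × 0.2) = 2.143; 2.143 − 1.282 = 0.861; power 80.5%. The loss rates below are assumptions, taken as equal in both arms.

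| Loss | Evaluable per arm | Sc. 1 | Sc. 2 | Sc. 3 | Sc. 4 |
|---|---|---|---|---|---|
| 0% | 50 | 80.5% | 84.8% | 95.7% | 88.8% |
| 5% | 47.5 | 79.0% | 83.3% | 95.0% | 87.6% |
| 10% | 45 | 77.4% | 81.8% | 94.1% | 86.2% |
| 20% | 40 | 73.7% | 78.3% | 92.0% | 83.0% |
| 33% | 33.3 | 68.0% | 72.7% | 87.9% | 77.6% |

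The 33% row is what surgery spread evenly over the 15 days would give (5/15). That ignores the four-week target, so it is an extreme illustration. Scenarios 2, 3 and 4 keep 80% down to 43, 26 and 37 evaluable per arm, that is, losses of 14%, 48% and 26%.

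**Allowance.** The 5% drop-out in Accrual and duration of study is applied to accrual time, not to the 50. The replacement rule covers withdrawals before completing treatment, so it does not clearly replace an adherent man with early surgery.

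**The case against.** A per-protocol primary analysis is a stated and reasoned choice for a pharmacodynamic window study, and an as-randomised analysis is already planned as secondary with its population defined. That stands; the choice in itself is not the fault.

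The dosing section can be read so that no adherent man is excluded. That also stands as a reading, but it works only by contradicting Table 5 and Interventions, so the passages still need reconciling. Interventions speaks of bringing surgery forward when clinically necessary. This suggests that early operations may be few, but the stated tolerance includes those days.

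A reader might infer that the primary comparison becomes tolerant metformin men against nearly all placebo men. The documents do not support that. The figure above 10% in Background concerns mild gastrointestinal discomfort with diarrhoea, not holds or reductions. The same section expects most patients to reach full dosing. Grade 1 events need no reduction, Grade 2 events are reduced only in limited circumstances, and a Grade 3 event allows restart at the same dose. Some held men can still qualify. Exclusion for early surgery is not shown to differ by arm, and under blinding there is no stated reason why it should.

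A reader might also infer that the trial misses its 80% power. That is not shown either. No loss rate is given, a 5% loss costs Scenario 1 about 1.5 points, and Scenarios 2–4 have reserve. If the replacement target of 90 applied and yielded 90 evaluable per arm, Scenario 1 power would be 94.4%; but that target conflicts with the 50 in Sample size.

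**Conclusion.** The inconsistency is established by the document's own figures. On the flow-chart window, 5 of 15 permitted surgery days make an adherent man non-evaluable. A man reduced before about Day 26 leaves the primary set. The withdrawal section applies a different 21-day rule. The possible imbalance between arms is a risk of unknown size, not a demonstrated bias. On power, the supportable statement is that 50 per arm has no margin in Scenario 1, so any material loss takes it below 80%: to 77.4% at an assumed 10% and 73.7% at an assumed 20%. These figures rest on equal losses in the two arms and on the plan's own effects and SDs. The point should be fixed because it decides who enters the primary analysis.

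**What to change.** Before unblinding:

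1. Reconcile Interventions, Dosing regimen, Table 5, Withdrawal of patients and Per protocol analysis so that they share one day count, one surgery window and one evaluability rule. Which schedule is intended is for the sponsor to state.
2. Word evaluability so that it admits every man who took study drug as scheduled and was operated inside the stated window, for example by defining it relative to scheduled doses. Simply counting escalation days toward the 21 is not enough: Day 21 surgery gives only 20 dosing days.
3. Report the planned as-randomised analysis, in all men with paired tissue, alongside the per-protocol result. Tabulate exclusions by arm and reason.
4. Restate power for the expected evaluable number, with the assumed loss given, and correct the replacement target of 90 against the 50. For reference, keeping 50 evaluable means randomising 50/(1 − loss): 53, 56 or 63 per arm at 5%, 10% or 20%.

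The cost is wording, a slightly lower stated power unless more men are recruited, and an evaluable set somewhat more varied in exposure.

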### Intention-to-treat population

The intention-to-Treat (ITT) population is defined as all patients who were randomised in this study. The ITT population will be analysed by treatment arm as randomised (i.e. treatment arm based on randomisation assignment).

### Safety analysis

The safety population is defined as all randomised patients who received at least 1 dose or partial dose of study drug. The safety population will be analysed by treatment arm as treated. The safety population will be used to conduct safety analyses.

### Exploratory analysis

Exploratory analysis by ^18^F Choline PET/MRI will be performed in five patients with MRI positive disease who will not be randomised and will all receive metformin. This patient population will be used to conduct exploratory analyses. Once five complete datasets are completed no further recruitment to this group will occur. Data will be summarised descriptively.

### Accrual and duration of study

The estimated accrual for this study is 10 patients a month. Allowing for a 5% drop out rate, patient accrual is expected to be completed within 18 months. We will account for all of the patients registered in the study. The number of patients who were not evaluable, who died or withdrew before treatment began will be specified. The distribution of follow-up time will be described and the number of patients lost to follow-up will be given.

## Methods: Monitoring

Neither the co-sponsors nor the investigators felt this study warranted a data monitoring committee (DMC) given the use of metformin which is a safe, well tolerated post licensed drug.

### Reporting responsibilities

Organisations have delegated the delivery of the Sponsor’s responsibility for Pharmacovigilance (as defined in Regulation 5 of the Medicines for Human Use (Clinical Trials) Regulations 2004 to the King’s Health Partners Clinical Trials Office (KHP-CTO).

All SAEs, SARs and SUSARs will be reported immediately by the Chief Investigator (and certainly no later than 24 h) to the KHP-CTO in accordance with the current Pharmacovigilance Policy. Death as a result of disease progression and other events that are primary or secondary outcome measures are not considered to be SAEs and should be reported in the normal way, on the appropriate CRF.

The KHP-CTO will report SUSARs to the regulatory authorities Medicines and Healthcare products Regulatory Agency (MHRA), competent authorities of other European Economic Area states in which the trial is taking place.

The Chief Investigator will report to the relevant ethics committee. Reporting timelines are as follows:SUSARs which are fatal or life-threatening must be reported not later than 7 days after the sponsor is first aware of the reaction. Any additional relevant information must be reported within a further 8 days.SUSARs that are not fatal or life-threatening must be reported within 15 days of the sponsor first becoming aware of the reaction.

The Chief Investigator and KHP-CTO (on behalf of the *co*-sponsors) will submit a Development Safety Update Report (DSUR) relating to this trial IMP to the MHRA and REC annually. Monitoring of this trial will be to ensure compliance with Good Clinical Practice and scientific integrity will be managed and oversight retained, by the KHP-CTO Quality Team.

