### Trial design

This is a randomised, placebo-controlled, double-blind, window of opportunity study investigating the biological mechanism of metformin in PCa. Patients with newly-diagnosed, early stage, prostate cancer scheduled for radical prostatectomy will either enter the main study and be randomised 1:1 to receive metformin (2 g daily over 2 divided doses; Arm A) or placebo four weeks prior to prostatectomy (standard of care; Arm B). A subset of five patients will enter the exploratory PET-MRI sub study. These five patients will all receive metformin and will undergo an additional two PET-MRI Scans (see below).

Patients with a history of a current or historical diagnosis of diabetes mellitus and/or prior metformin use will be excluded.

The primary objective of this study is to investigate the biological mechanism of metformin on PCa using pharmacodynamic markers (Table 1). The primary endpoint for this study is the difference in expression levels of biomarkers representing the FASN/AMPK pathway for the metformin and placebo groups, as measured by the H score. Secondary endpoints include the difference in indicators of proliferation in the same groups, as well as differences in expression levels of the biomarkers between benign and malignant tissue (Table 1).

**Table 1 Tab1:** Objectives

Objectives	Endpoints
Primary endpoints	
To determine the biological effect of metformin on markers of the FASN/AMPK pathway in prostate tissue by comparison of pre and post-treatment samples.	Assessment of the difference in expression levels of markers of the FASN/AMPK pathway pre and post treatment between the placebo and metformin arms.
Secondary endpoints	
To evaluate the biological effect of metformin on markers of proliferation in prostate tissue by comparison of pre and post-treatment samples.	Assessment of the difference in expression levels of indicators of proliferation (ki67 and Terminal deoxynucleotidyl transferase dUTP nick end labelling (TUNEL)) pre and post treatment between the placebo and metformin arms.
To evaluate differences in FASN/AMPK-associated markers in benign and malignant prostate tissue.	Assessment of the difference in expression levels of markers of the FASN/AMPK pathway and indicators of proliferation between benign and malignant prostate tissue in the placebo and metformin arms.
To measure metformin levels in prostate tissue.	Assessment of the difference in metformin levels in baseline and post-treatment prostate tissue.

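### The SAE exemption for outcome measures takes in surgical harms that Table 1 makes secondary endpoints, so serious cases can leave the 24-hour reporting route

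*Protocol article*

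**What the plan says.** Reporting responsibilities (Methods: Monitoring) sets the expedited rule first: "All SAEs, SARs and SUSARs will be reported immediately by the Chief Investigator (and certainly no later than 24 h) to the KHP-CTO". The next sentence carves out two things: death from disease progression, and a general class, namely that "other events that are primary or secondary outcome measures are not considered to be SAEs". Events in either group "should be reported in the normal way, on the appropriate CRF". The same section then gives the 7-day and 15-day timelines for SUSARs.

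Table 1 (Trial design) defines the outcome measures. Its block headed "Secondary endpoints" runs down to the exploratory heading. Two of its rows concern safety. One has the endpoint "Assessment of adverse events and laboratory evaluations". The other has the endpoint "Assessment of surgical-specific toxicities: time between biopsy and surgery, peri-operative bleeding, infection, rectal injury and length of hospital stay".

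On oversight, Methods: Monitoring says: "Neither the co-sponsors nor the investigators felt this study warranted a data monitoring committee".

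**The concern.** An exemption for outcome events makes sense where the outcomes are disease events that would otherwise flood the expedited route. Here the safety events are themselves listed as secondary outcomes. A site that follows the sentence as printed could therefore treat a serious post-operative bleed, infection or rectal injury as exempt because it appears in Table 1, and enter it on a CRF without telling the trials office within 24 hours.

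Two things are at stake. One is speed: how soon anyone outside the site learns of a serious event in men who take study drug until the evening before surgery. The other is classification: whether an event that the document says is not an SAE is ever assessed for seriousness and causality. The absence of a data monitoring committee means one fewer body looking at accumulating safety data, but this is a minor point, because such a committee does not replace expedited reporting.

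**Working it through.** No calculation in the plan bears on this. The check sets the exemption against the endpoint list and the visit schedule.

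**Step 1: which outcome measures are clinical events?** Taking the primary and secondary rows of Table 1 in order:

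| Table 1 row | Type of measure | Could it be an SAE? |
|---|---|---|
| FASN/AMPK markers (primary) | Tissue measurement | No |
| Ki67 and TUNEL | Tissue measurement | No |
| Benign versus malignant tissue | Tissue measurement | No |
| Tissue metformin level | Tissue measurement | No |
| Safety: adverse events, laboratory evaluations | Safety assessment | Yes, if serious |
| Surgical toxicity: bleeding, infection, rectal injury | Named clinical harms | Yes, if serious |
| Surgical toxicity: biopsy-to-surgery time, length of stay | Durations | Not events in themselves |

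Death from disease progression is exempted separately and by name. The general clause can therefore add only events from the two safety rows. It has no efficacy-type event to act on.

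**Step 2: narrow reading.** Suppose the clause covers only events that Table 1 names specifically. That gives three: peri-operative bleeding, infection and rectal injury. Serious cases of these are then not SAEs and go on the CRF.

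**Step 3: broad reading.** Suppose the safety row makes every adverse event an outcome measure. Every possible SAE is then exempt, and the 24-hour duty in the preceding sentence has nothing left to apply to.

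**Step 4: what the CRF route means in time.** Table 5 marks adverse events at baseline, day 21, the pre-surgery visit and the post-operative visit. The surgery column has no adverse-event mark. The first scheduled adverse-event and Clavien-Dindo assessment after the operation is therefore at 8-10 weeks: 8 × 7 = 56 days to 10 × 7 = 70 days, against 1 day on the expedited route. A CRF entry could be made earlier, but no scheduled assessment prompts it.

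**Step 5: how many men.** 50 + 50 randomised plus 5 in the imaging sub-study = 105, all scheduled for prostatectomy. The document gives no complication rates, so the number of events affected cannot be stated.

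**The case against.** The strongest reply is that the clause is narrower in effect than it looks.

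- **The broad reading is strained.** The endpoint is an assessment of adverse events and names no event, and the reading would empty the sentence before it. The article's Background also describes lactic acidosis as a serious adverse event. This stands: a reader might infer that every adverse event, lactic acidosis included, escapes SAE status, but the document does not support that as its intended meaning.
- **Reaction reporting survives.** The clause exempts SAEs only. SARs and SUSARs are listed separately, and the 7-day and 15-day duties carry no exception. This stands too: it would be wrong to conclude that an exempt event can never become a SUSAR. What remains is a gap. The text does not say how an event it does not consider an SAE would enter seriousness and causality assessment.
- **The data are kept.** Adverse events are graded by CTCAE and surgical complications by Clavien-Dindo, and exempt events are entered on the CRF. This stands: a reader might infer that safety data would be lost, but the effect is on what is classed as serious, and when it is known.
- **Complications of planned surgery may be exempt on purpose.** That is possible, but the article does not say so. The reason it gives for exemption is that an event is an outcome measure, not that it is an expected surgical complication.
- **A condensed article and an unseen pharmacovigilance policy may resolve it.** The policy is cited for the 24-hour rule, while the exemption is printed without qualification. The point does not rest on an omission: two statements in the same document conflict. How sites act in practice under the policy cannot be judged from here.

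**Conclusion.** The concern holds in limited form. As printed, the exemption conflicts with Table 1, and following it takes at least serious peri-operative bleeding, infection and rectal injury off the 24-hour SAE route. Their next scheduled assessment is about two months after surgery. This is a wrongly drawn rule, not missing detail.

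The harm is to the timeliness and classification of serious events. It falls most clearly on surgical complications not attributed to the drug, since reaction reporting stays in force. The size is three named categories of harm among up to 105 men having surgery; length of stay is a duration and does not make a fourth.

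This rests on two assumptions: that sites apply the sentence as written, and that no overriding definition sits in the full protocol or the pharmacovigilance policy, neither of which is shown.

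**What to change.** In Reporting responsibilities, delete the limb of the sentence that extends the exemption from death due to disease progression to outcome measures generally. Alternatively, replace it with an explicit, closed list of exempt events, reconciled with Table 1, so that no safety endpoint is exempt merely because it is an outcome. If the sponsor does intend some surgical complications to bypass the 24-hour route, the list should name them and say how they are assessed for seriousness and causality.

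The cost is a one-sentence amendment and some additional SAE reports. Endpoints, sample size and visit schedule are unaffected.
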